### **Introduction**

This data analysis plan describes the outcomes, comparisons and methods that will be used for the functional genomics analysis of vitamin D supplementation involving the BEST-D clinical trial ([www.bestdtrial.org](http://www.bestdtrial.org)). This is focused on genetic association, gene expression and integrated analysis. These analyses will be carried out by the [name] group and CGAT in collaboration with the Clinical Trial Service Unit, all at the University of Oxford.

### **Context of the BEST-D trial**

The Biochemical Efficacy and Safety Trial of Vitamin D is a dose-finding trial assessing the biochemical and vascular effects of high dose vitamin D. The rationale, design and protocol are described elsewhere. Below we briefly describe the rationale of the functional genomics analysis of the BEST-D trial.

### **Functional genomics and molecular analysis in BEST-D**

#### Background

Although animal and experimental models are informative, recent studies have highlighted the difficulty of translating such research findings to humans, particularly in the context of complex diseases (Seok, Warren et al., 2013; Gentile, Nacionales et al., 2014). Higher than expected negative results in clinical trials, exemplified by sepsis (Annane, 2009), have emphasized the need to better understand physiopathological processes and mechanisms of action of drugs.

Randomised clinical trials provide one of the best designs to assess causality and by-pass the difficulties of translating findings from experimental models. Clinical trials are rarely coupled to detailed molecular analysis however and incomplete knowledge of target molecules may cause efficacy trials to result in inconclusive findings. Furthermore, it is known that functional regulatory genetic variation can play a determining role in individual susceptibility to disease (Visscher, Brown et al., 2012) and to drug response (Qiu, Rogers et al., 2014) by modulating RNA expression (Lee, Ye et al., 2014; Fairfax, Humburg et al., 2014). Recently, clinical trial studies have begun using transcriptome comparisons to aid mechanistic understanding and biomarker identification (Beck, Thaci et al., 2014). To our knowledge, no trial has previously studied the impact of genetic variation in response to vitamin D

supplementation and very few studies have assessed the genetics of induced gene expression in clinical trials (Qiu, Rogers et al., 2014).

The aim of functional genomics is to understand how genomes and their products relate to the organism's phenotype. Recent technological and scientific advancements in this field now make it possible to study molecular mechanisms at unparalleled scale. Genome-wide genotyping and gene expression profiling combined with complementary biochemical analysis can be used as global measures of systemic response and mechanism search. These genomic and molecular measures can be associated with phenotypic data to provide an integrated analysis that may yield clinically relevant insights.

Highly interdisciplinary and collaborative efforts are necessary in order to design and execute studies requiring careful sample and data collection for functional genomics analysis in the context of randomised clinical trials. The functional genomic analysis of vitamin D supplementation in BEST-D study is a unique effort to explore how basic science research can work in tandem with large-scale trials. Its aim within the context of the trial is to understand how response to an intervention varies between individuals and treatment groups and to provide insight into the mechanisms of action of vitamin D.

Vitamin D is well known for its classic role in calcium metabolism with deficiency associated with bone disease while there is accumulating evidence pointing to its importance in vascular and immune/inflammatory disorders (Bouillon, Carmeliet et al., 2008; Fraser and Kodicek, 1970; Brumbaugh and Haussler, 1975). Indeed over the last several years it has become clear that vitamin D has multi-system effects and is an important modulator of innate and adaptive immunity with anti-inflammatory actions.

#### Aim of the functional genomics and molecular analysis in BEST-D study

The overall aim of this study is to investigate the effects of low and high dose vitamin D supplementation on genome-wide gene expression and how this is modulated by genetic variation. To do this, we propose adopting a functional genomics approach to analyse study participants in the BEST-D clinical trial (placebo, low dose or high dose supplementation over a 12-month treatment period).

1. We will measure changes in genome-wide gene expression and blood markers of immunity and inflammation, correlate this with 25(OH)D concentrations and use systems biology approaches to investigate differentially expressed genes, pathways and functional responses.
2. We will investigate the impact of vitamin D supplementation on the functional effects of regulatory genetic variation by mapping gene expression quantitative trait loci (eQTL) in different contexts (placebo, low dose and high dose vitamin D supplementation) and interrogate phenotypic relationships.
3. We will assess the feasibility of carrying out RNA and DNA analysis in the context of a randomised, double-blinded, placebo controlled trial.

#### Hypothesis of the BEST-D trial and of the molecular effects of vitamin D supplementation

Vitamin D exerts effects in several essential biological processes and perturbations in these may contribute to pathophysiology (Bouillon, Bischoff-Ferrari et al., 2008). Causal evidence is generally lacking but it is possible that vitamin D contributes to the control of vascular calcification, arterial stiffness and/or cardiac hypertrophy

through the regulation of parathyroid hormone (Holick, 2007; Bouillon, Bischoff-Ferrari et al., 2008). It is also proposed that the immune and inflammatory modulating effects of vitamin D may be relevant in both vascular (Wong, Leisegang et al., 2014) and non-vascular disease (Donate-Correa, Dominguez-Pimentel et al., 2014; Busse, Bale et al., 2013).

In the context of inflammation, we hypothesise that vitamin D produces beneficial effects by reducing chronic inflammation and this can be measured in blood cells through molecular biomarkers. Following vitamin D supplementation, we anticipate a shift in the transcriptomic profile of participants, in particular in relation to pro- and anti-inflammatory molecules and other associated molecules.

Previous studies have investigated the relationship of vitamin D to gene expression (Carlberg, 2014; Hossein-nezhad, Spira et al., 2013). These have generally been in experimental models, cross-sectional studies or in studies with small sample sizes. The present investigation will use a randomised trial design, the BEST-D trial, to relate changes in plasma 25(OH)D to changes in gene expression in healthy older people as well as to genetic variation, biochemical measures and phenotypic information.

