### Design

The BEST-D design is a double blind, randomised, placebo controlled trial with before and after and group comparisons for supplementation with 2000 IU and 4000 IU of vitamin D with 100 participants in each group. The primary efficacy assessment is of intention to treat. As part of the BEST-D trial, samples for DNA, RNA and plasma measurements were obtained from participants together with physiologic, phenotypic and safety measures as described separately in the BEST-D trial protocol. Samples for DNA and RNA analyses will be obtained at baseline (0) and 12 months.

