### Outcomes

- a. Primary outcomes
  - Genome-wide differential gene expression for peripheral blood leukocytes following vitamin D supplementation (profiling at baseline and 12 months, resolution of differentially expressed genes);
  - Genome-wide single nucleotide (SNP) genotyping of study cohort (baseline);
  - eQTL mapping of local (likely cis-acting) and distant (trans-acting) SNP markers associated with gene expression in different contexts of vitamin D supplementation.
- b. Secondary outcomes
  - Pathway and systems biology analysis of differentially expressed genes associated with vitamin D supplementation and co-expression gene modules;
  - Analysis of genotype-transcriptome-plasma 25(OH)D associations;
  - Analysis of quantitative trait loci (QTL) for plasma levels of 25(OH)D in BEST-D participants using genetic variants previously associated by genome-wide association studies (Wang, Zhang et al., 2010; Ahn, Yu et al., 2010);
  - Analysis of molecular associations between genotype, gene expression, plasma 25(OH)D and pre-specified plasma measurements (PTH, calcium, albumin, phosphate, creatinine, alkaline phosphatase, total cholesterol, LDL-C, HDL-C, triglycerides, apolipoprotein A, apolipoprotein B, hsCRP and NT-proBNP). These will be primarily carried out for concurrent measurements (i.e. for those at

baseline and 12 months). See also the protocol and data analysis plan for BEST-D;

- Analysis of the association between molecular measurements and pre-specified phenotype measurements including fractures, respiratory infections, body mass index, bone density measurements, glomerular filtration rate and urinary albumin/creatinine ratio;
  - Measurement of pro- and anti-inflammatory cytokines prioritised by the mRNA profiling described in the primary outcome.
- c. Tertiary outcomes
- Quantitative trait locus (QTL) analysis of pre-specified plasma measurements for those mentioned above;
  - Analysis of association of molecular and physiologic measures including systolic and diastolic blood pressure, heart rate, and arterial stiffness measured at 12 months;
  - Analysis of association of molecular and echocardiographic measures for a pre-specified sub-group at 12 months.

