### Details of analyses

#### a. Analysis methods overview

Our analysis follows the BEST-D data analysis plan and will carry out comparisons as intention-to-treat analyses. The main analyses at each stage are outlined below. Methods are intricate and evolving however and several stages are dependent on the particular characteristics and quality of the acquired measurements. Here we only provide a brief overview of the general steps that will be taken at each stage.

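### The plan credits the randomised design with relating change in 25(OH)D to change in expression, but achieved 25(OH)D is not randomised and the SAP does not say how allocation enters that analysis

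*SAP*

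**What the plan says.** Two places announce the analysis. The SAP's Hypothesis section, having noted the limits of earlier studies (experimental models, cross-sectional designs, small samples), states that the randomised trial design will be used to "relate changes in plasma 25(OH)D to changes in gene expression in healthy older people as well as to genetic variation". Item 1 of the Aim section names the method as correlation: "We will measure changes in genome-wide gene expression and blood markers of immunity and inflammation, correlate this with 25(OH)D concentrations".

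The Outcomes section ranks this work as secondary: "Analysis of genotype-transcriptome-plasma 25(OH)D associations". The primary expression outcome is a different one: "Genome-wide differential gene expression for peripheral blood leukocytes following vitamin D supplementation". The Comparisons section sets contrasts by allocation for it (each dose against placebo, dose against dose), alongside comparisons of each dose with baseline. The analysis overview says the study "will carry out comparisons as intention-to-treat analyses".

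The Covariates section lists sex, age, BMI, dietary calcium, disease history and blood cell counts, and adds principal components for batch and hidden effects. It does not list allocation, adherence, season or baseline 25(OH)D. Baseline 25(OH)D appears only in the tertiary comparison of the primary outcomes.

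**The concern.** Randomisation protects a comparison of arms. It does not protect a regression of one post-randomisation change on another. Two participants on the same dose may differ in their 25(OH)D rise because one took the capsules more regularly or spent more time in the sun, and such differences may also go with leukocyte expression. That within-arm part of the relation is observational, much like the cross-sectional work with which the Hypothesis section contrasts this study.

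If the analysis runs as worded, genes could be reported as related to 25(OH)D with the authority of a randomised trial when some of the association comes from confounding. Those genes could then feed the discussion of how vitamin D acts.

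**Working it through.** **Figure in the plan.** The SAP gives no model, power or error rate for this analysis, so there is nothing to reproduce.

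**What the text fixes.** The Hypothesis and Aim sections name the exposure (25(OH)D), the response (change in expression) and the operation (relate, correlate). No section says whether the analysis is pooled across arms or made within arms, or whether allocation is in the model. The Comparisons section sets changes within arm and contrasts between arms for secondary outcomes, but neither defines a model with 25(OH)D as a continuous exposure.

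**Illustration of scale.**

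- From the SAP: "supplementation with 2000 IU and 4000 IU of vitamin D with 100 participants in each group"; with placebo, three arms and n = 300.
- Assumed: mean 25(OH)D change by arm of 0/40/70 or 0/50/80 nmol/L; within-arm SD of 20 to 30 nmol/L; no true effect; a confounded within-arm correlation r left after adjustment; a two-sided 5% test per gene.

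The share of the variance of 25(OH)D change that lies within arms is w = SD² / (V + SD²), where V is the variance of the three arm means.

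- Low end, means 0/50/80 and SD 20: V = 1,088.9, so w = 400 / 1,488.9 = 0.27.
- High end, means 0/40/70 and SD 30: V = 822.2, so w = 900 / 1,722.2 = 0.52.

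For a pooled correlation the expected z is r × √w × √300, and the rejection rate is Φ(z − 1.96) + Φ(−1.96 − z).

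| r | w | z | rejection under no effect |
|---|---|---|---|
| 0.1 | 0.27 | 0.90 | 15% |
| 0.1 | 0.52 | 1.25 | 24% |
| 0.2 | 0.27 | 1.80 | 43% |
| 0.2 | 0.52 | 2.50 | 71% |

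Using allocation as instrument keeps only the between-arm share, 1 − w. The standard error therefore grows by about 1/√(1 − w): 1/√0.73 = 1.17 to 1/√0.48 = 1.44.

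**Cross-check by simulation.** Three arms of 100, 3,000 replicates per scenario, no true effect, other assumed inputs (mean changes 0/30/60 or 0/50/80 nmol/L; within-arm SD 15, 25 or 35).

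| r | pooled | within arm | allocation as instrument |
|---|---|---|---|
| 0 | 0.04–0.05 | about 0.05 | 0.04–0.06 |
| 0.1 | 0.13–0.28 | 0.40–0.42 | 0.04–0.06 |
| 0.2 | 0.30–0.81 | 0.93–0.94 | 0.04–0.05 |

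In these scenarios 33% to 83% of the variance of 25(OH)D change came from allocation. A pooled correlation is thus only partly exposed to confounding; a within-arm correlation carries it in full.

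**The case against.** The case against is substantial, and most of it stands.

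- **The sentence is background prose and makes no causal claim.** The SAP never calls the correlation causal, and the Outcomes section already speaks of associations. A reader might infer that the plan presents the correlation as a causal estimate; the document does not say so. What remains is that the Hypothesis section attributes the relation to the randomised design and that no section limits what it can support.
- **The causal question has its own analysis.** The primary comparisons include between-arm contrasts under intention to treat. A reader might infer that the trial's main expression results are confounded; for those contrasts nothing supports this.
- **Adjustment is planned.** BMI, cell counts and principal components are listed, and the microarray section provides for control of confounding. These reduce the problem, but need not remove confounding by adherence or sun exposure.
- **Multiplicity correction is planned.** The illustration uses an unadjusted 5% test, whereas the SAP plans false-discovery-rate or Bonferroni-type correction. That would lower the rejection rates, but it limits chance findings and does not remove confounded associations.
- **An instrument adds little to detection.** Its test of no effect largely repeats the arm comparison. It also sets aside within-arm differences, although variation in response between individuals is one of the plan's interests. It therefore cannot replace the association analysis; what it adds is an effect per nmol/L.

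**Conclusion.** The concern holds for the secondary analysis of 25(OH)D and expression. Achieved 25(OH)D is a post-randomisation variable, its within-arm variation may be confounded beyond the planned adjustment, and the SAP specifies neither the model nor the role of allocation. The primary inference is not affected where it rests on the between-arm contrasts.

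Only the direction is firm: residual within-arm confounding pushes the false-positive rate above its nominal level. The sign of the bias for any one gene is unknown. Every input to the rejection rates except the sample size is assumed. A reader might take 15% to 24% as the share of genes that would be falsely reported. The documents do not support that: it is a per-gene probability, on condition that the gene carries a residual correlation of 0.1 after adjustment, before multiplicity correction, in a pooled test that the SAP does not specify.

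This is a worthwhile and inexpensive improvement to a secondary analysis, not a flaw in the trial's main comparisons.

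**What to change.** In the SAP's account of the secondary 25(OH)D and expression analysis:

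1. State the change-on-change model: pooled or within arm, which covariates, and how allocation enters.
2. Report its result as an observational association.
3. Keep causal statements to the between-arm contrasts, and align the Hypothesis sentence with this.
4. Where an effect per nmol/L of 25(OH)D is reported, add two-stage least squares with the two allocation indicators as instruments for the change in 25(OH)D, adjusted for baseline expression and baseline 25(OH)D.
5. State the assumptions of that estimate: allocation acts on expression only through 25(OH)D, and the effect is linear and common across doses.

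The cost is a few sentences and one standard model on measurements already planned. The instrumented intervals will be wider than those of the plain regression (about 1.17 to 1.44 times under the assumptions above), and its test of no effect will largely repeat the arm comparisons.

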### Design

The BEST-D design is a double blind, randomised, placebo controlled trial with before and after and group comparisons for supplementation with 2000 IU and 4000 IU of vitamin D with 100 participants in each group. The primary efficacy assessment is of intention to treat. As part of the BEST-D trial, samples for DNA, RNA and plasma measurements were obtained from participants together with physiologic, phenotypic and safety measures as described separately in the BEST-D trial protocol. Samples for DNA and RNA analyses will be obtained at baseline (0) and 12 months.

### Outcomes

- a. Primary outcomes
  - Genome-wide differential gene expression for peripheral blood leukocytes following vitamin D supplementation (profiling at baseline and 12 months, resolution of differentially expressed genes);
  - Genome-wide single nucleotide (SNP) genotyping of study cohort (baseline);
  - eQTL mapping of local (likely cis-acting) and distant (trans-acting) SNP markers associated with gene expression in different contexts of vitamin D supplementation.
- b. Secondary outcomes
  - Pathway and systems biology analysis of differentially expressed genes associated with vitamin D supplementation and co-expression gene modules;
  - Analysis of genotype-transcriptome-plasma 25(OH)D associations;
  - Analysis of quantitative trait loci (QTL) for plasma levels of 25(OH)D in BEST-D participants using genetic variants previously associated by genome-wide association studies (Wang, Zhang et al., 2010; Ahn, Yu et al., 2010);
  - Analysis of molecular associations between genotype, gene expression, plasma 25(OH)D and pre-specified plasma measurements (PTH, calcium, albumin, phosphate, creatinine, alkaline phosphatase, total cholesterol, LDL-C, HDL-C, triglycerides, apolipoprotein A, apolipoprotein B, hsCRP and NT-proBNP). These will be primarily carried out for concurrent measurements (i.e. for those at

baseline and 12 months). See also the protocol and data analysis plan for BEST-D;

- Analysis of the association between molecular measurements and pre-specified phenotype measurements including fractures, respiratory infections, body mass index, bone density measurements, glomerular filtration rate and urinary albumin/creatinine ratio;
  - Measurement of pro- and anti-inflammatory cytokines prioritised by the mRNA profiling described in the primary outcome.
- c. Tertiary outcomes
- Quantitative trait locus (QTL) analysis of pre-specified plasma measurements for those mentioned above;
  - Analysis of association of molecular and physiologic measures including systolic and diastolic blood pressure, heart rate, and arterial stiffness measured at 12 months;
  - Analysis of association of molecular and echocardiographic measures for a pre-specified sub-group at 12 months.

### Comparisons

- a. Primary comparisons of the primary outcomes:
- All participants allocated 100 µg (4,000 IU) vitamin D3 daily (data collected at 12 months) vs. baseline;
  - All participants allocated 100 µg (4,000 IU) vitamin D3 daily vs. all participants allocated placebo.
  - All participants allocated 100 µg (4,000 IU) vitamin D3 daily vs. all participants allocated 50 µg (2,000 IU) vitamin D3 daily;
  - All participants allocated 50 µg (2,000 IU) vitamin D3 daily vs. baseline
  - All participants allocated 50 µg (2,000 IU) vitamin D3 daily vs. participants allocated placebo.
- b. Secondary comparisons of the primary outcomes:
- Participants allocated any active vitamin D3 dose (50 µg or 100 µg daily) versus participants allocated placebo.
- c. Tertiary comparison of the primary outcomes:
- All participants (4,000 IU, 2,000 IU and placebo) will be analysed according to treatment allocation separately using the following covariates (baseline characteristics):
- Sex
  - Age (<70, ≥70 years)
  - BMI (<25, ≥25 to <30, ≥30 kg/m^2)
  - Plasma 25(OH)D concentrations (<25, ≥25 to <50, ≥50 nmol/L)
  - Dietary calcium intake (<800, ≥800 to <1000, ≥1000 mg/day)
  - Estimated glomerular filtration rate (eGFR) (<60, ≥60 to <90, ≥90 ml/min/1.73 m^2)
  - Prior history of cardiovascular disease
  - Prior history of cancer

Although intervals have been assigned for some variables, continuous data will be used where appropriate. A generalized linear model for gene expression and

baseline characteristics will be used as part of this analysis as described in similar studies (Smyth, 2004) and specified below.

- d. Comparisons of secondary and tertiary outcomes will include:
- Changes from baseline within each treatment allocation;
  - Participants allocated 100 µg vitamin D3 daily vs. participants allocated placebo;
  - Participants allocated 50 µg vitamin D3 daily vs. participants allocated placebo;
  - Participants allocated any active vitamin D3 dose (50 µg or 100 µg daily) vs. participants allocated placebo;
  - In some instances, comparisons will be made between vitamin D3 dose groups to understand dose responses.

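### Two within-arm changes from baseline rank as primary alongside the randomised contrasts, with no placebo change listed for the primary outcomes and no rule for attributing effects to vitamin D

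*SAP*

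**What the plan says.** Under Design, the SAP describes a "randomised, placebo controlled trial with before and after and group comparisons", with 100 participants per group and RNA sampled at baseline and 12 months.

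Under Comparisons, part a, five comparisons are primary for the primary outcomes:

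- 4,000 IU "daily (data collected at 12 months) vs. baseline"
- 4,000 IU "daily vs. all participants allocated placebo"
- 4,000 IU against 2,000 IU
- 2,000 IU "daily vs. baseline"
- 2,000 IU "daily vs. participants allocated placebo"

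Part b adds pooled active dose against placebo. Part c states that "All participants (4,000 IU, 2,000 IU and placebo) will be analysed according to treatment allocation separately", by baseline characteristics; it names no placebo contrast over time. Part d includes "Changes from baseline within each treatment allocation", which covers placebo, but it applies to secondary and tertiary outcomes only.

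No sentence ranks the five primary comparisons or says which prevails if a before-after result and a placebo contrast disagree. Nor does the section say whether the between-arm contrasts use 12-month values, changes, or 12-month values adjusted for baseline.

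**The concern.** A change from baseline within one arm is not a randomised comparison. It is the sum of any vitamin D effect and whatever else differs between the two visits: a year of ageing, and any difference in how or when samples were collected and how long they were stored. The SAP's Background gives causal assessment as the reason for working inside a randomised trial, yet two of its five primary comparisons lack that protection.

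The list is also lopsided. It includes the change in each active arm but not the placebo change that a reader would need to interpret them. A gene whose expression moves equally in all three arms could meet the plan's primary criterion in both dose groups and look like a finding replicated across doses.

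There is one clear onward route. Under Outcomes, the cytokines to be measured are chosen from the primary mRNA profiling, so a time-driven gene list could steer that choice.

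**Working it through.** The SAP states no power, effect size or error rate for these comparisons, so there is no figure of its own to reproduce.

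**Count.** Of the five primary comparisons, 2 are within-arm and uncontrolled, 2 are dose against placebo, and 1 is dose against dose. No placebo 12-month change is listed in part a or part b.

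**What each contrast estimates.** Let τ be the drug effect and δ a time shift common to all arms.

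- Active arm, 12 months minus baseline: τ + δ
- Placebo arm, 12 months minus baseline: δ
- Active change minus placebo change: (τ + δ) − δ = τ

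With τ = 0, the before-after test has mean δ and the controlled contrast has mean 0.

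**Inputs.** n = 100 pairs per arm (Design). The 5% adjusted threshold comes from the section on pathway, network and co-expression analyses, and Benjamini-Hochberg is one of the methods named in the multiplicity section. Drift size, number of drifting probes, total probes and independence between probes are assumptions; the SAP gives none of them.

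**Per-probe rejection, no drug effect.** Express δ in SDs of the within-person change. The paired t statistic has 99 degrees of freedom and non-centrality δ√100 = 10δ, and the two-sided 5% critical value is 1.984.

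| δ (SD) | non-centrality | P(reject), p<0.05 | P(reject), p<0.001 |
|---|---|---|---|
| 0 | 0 | 5.0% | 0.1% |
| 0.1 | 1 | 16.8% | 1.0% |
| 0.2 | 2 | 50.8% | 8.9% |
| 0.3 | 3 | 84.4% | 35.5% |

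The difference in change between active and placebo stays at the nominal level in every row. If the arms are independent, both active arms reject at p<0.05 with probability 0.508² = 26% at 0.2 SD and 0.844² = 71% at 0.3 SD. That is how a common drift could pass for replication.

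**After multiplicity control.** The plan adjusts p-values, so the table above overstates the number of genes that would be called. Simulation with 2,000 drifting probes, no drug effect and Benjamini-Hochberg at 5% gives these mean calls per active arm (300 runs):

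| Total probes | 0.1 SD | 0.2 SD | 0.3 SD |
|---|---|---|---|
| 10,000 | 0.5 | 175 | 1,203 |
| 20,000 | 0.3 | 76 | 959 |
| 40,000 | 0.1 | 29 | 722 |

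The placebo-controlled change gave fewer than 0.1 calls per run in every cell.

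With only 1,000 of 20,000 probes drifting, a separate five-run simulation gave about 13 calls at 0.2 SD and 364 at 0.3 SD. The adjustment limits chance findings. It does not treat a real shift over time as false, because for a before-after null hypothesis that shift is a true departure.

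**The case against.** The strongest reply is that the plan already holds the remedy. Both doses against placebo are primary, pooled active dose against placebo is secondary, and both time points are collected in every arm. A shared drift would appear in the before-after lists and be absent from the placebo contrasts. Before-after comparison is an openly declared design feature, and no sentence says that such a result alone establishes a drug effect. This is also a mechanistic, exploratory plan. All of that stands, and it makes the problem one of status and interpretation, not of a missing control. It does not supply the missing rule on which primary result prevails.

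Four stronger readings are tempting and should be resisted:

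- **That the plan has nothing to set against the active-arm changes, or that drift will be read as a drug effect.** The placebo contrasts are primary, so this is a risk and not a certainty. Placebo change is also listed, though only for secondary and tertiary outcomes.
- **That batch effects are ignored.** The Covariates section plans randomised sample order on the arrays, principal components for batch and hidden effects, and total and differential cell counts. These reduce array batch effects. They do not remove ageing or collection and storage differences tied to visit, and components that track visit could absorb real change too.
- **That the eQTL results inherit the problem.** The eQTL section does not start from the before-after gene list. Within one context, a uniform shift in expression moves the intercept and not the SNP slope.
- **That a 0.2 SD drift in 2,000 probes yields about 1,000 false genes.** That is 2,000 × 0.508 at unadjusted p<0.05. Under the planned type of adjustment the figure is about 30 to 175.

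The pathway analyses are secondary outcomes, compared within every arm and against placebo, so they too are better protected than the primary list suggests.

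**Conclusion.** The point holds in a limited form. Two of the five primary comparisons are uncontrolled, they carry the same rank as the randomised contrasts, the matching placebo change is not listed for the primary outcomes, and there is no attribution rule. A team following the text exactly could report primary differentially expressed genes that reflect the passage of a year.

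The size cannot be fixed from the SAP. Under the stated assumptions it runs from negligible at 0.1 SD to several hundred or more than a thousand probes at 0.3 SD. It depends almost wholly on the assumed drift and on how many probes share it. The cancellation in the placebo contrast requires the drift to be common to all arms, which randomisation and blinding make reasonable. This deserves correction because the remedy is cheap, and not because the trial lacks a valid comparison.

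**What to change.** In Comparisons, part a:

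1. Keep as primary inferential comparisons for gene expression only the randomised contrasts: each dose against placebo, and 4,000 IU against 2,000 IU.
2. State that each uses 12-month expression adjusted for the participant's own baseline expression, or an arm-by-time term in a model for both visits. This also settles what the between-arm contrasts measure.
3. Report 12-month changes from baseline in all three arms, placebo included, as descriptive.
4. Add one sentence: attribution of an expression change to vitamin D rests on the placebo contrasts. Apply the same rule when choosing cytokines.

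A smaller alternative is to leave the two before-after lines in place, add the placebo change beside them, and include the sentence in item 4. That supplies the missing comparator and rule but leaves uncontrolled contrasts labelled primary.

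How the remaining contrasts are grouped for multiplicity is a separate question that this point does not decide.

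The cost is SAP wording only, with no new samples or data. The downside is that the before-after gene lists lose primary status.
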